## Methods

### Trial design and study setting

The proposed trial is a monocentric, randomized, double-blind, placebo-controlled, 1:1 parallel-group 7-month clinical trial comparing the effects of a high dose of psilocybin (30 mg) to those of a low dose of psilocybin (5 mg, active placebo) in 62 participants with sAUD. The trial will be conducted at the Psychiatry Department of the Brugmann University Hospital. Recruitment will start in winter 2024, and we expect completion of the study in autumn 2026. Our protocol adheres to the SPIRIT guidelines (Standard Protocol Items: Recommendations for Interventional Trials [67]).

### Trial population

Sixty-two participants will be included, with 31 participants receiving the experimental treatment (psilocybin high dose: 30 mg) and 31 participants receiving the active placebo (psilocybin low dose: 5 mg).

#### Sample size

In line with extant studies indicating medium to large effects of PAT on alcohol consumption in patients with AUD (Cohen’s d = 1, [54]; Hedges’ g = 0.52 [15]), the sample size was calculated to observe a medium-size effect (Cohen’s f = 0.25) with a power of 0.9 and a type I error set at 0.05. A priori power calculation based on the primary clinical hypothesis (mixed-design analysis of variance, two groups: high dose vs. active placebo; two timepoints: % heavy drinking days from 8 weeks prehospitalization to 1 day prehospitalization vs. % heavy drinking days from hospital discharge to 4 weeks posthospital discharge) indicated a needed sample size of *n* = 46. Accounting for 25% attrition, we set the total sample size to *n* = 62. If the drop-out rate is higher, we will continue to include participants until 46 have completed visit 14 (primary clinical outcome).

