#### Psychological mechanisms - alcohol-related parameters

The first contemporary pilot trial of PAT for AUD [54] revealed decreased craving for alcohol and both increased motivation to change alcohol consumption behavior and abstinence self-efficacy following PAT. While encouraging, these effects need to be replicated in RCTs with larger samples.

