### Outcomes

#### Primary clinical outcome

The primary clinical outcome is the difference between the two treatment arms in terms of change from baseline (8 weeks to 1 day pre-enrollment) to 4 weeks posthospital discharge (1 day to 4 weeks postdischarge) in the percentage of heavy drinking days, defined as ≥ 5 standard drinks/60 g of alcohol for males and ≥ 4 standard drinks/48 g of alcohol for females [15]. A reduction in heavy drinking days yields clinically significant health ameliorations [94], matches the treatment objectives of numerous patients [95] and is recognized by the European Medicines Agency as an adequate measure of efficacy [96]. Moreover, previous results suggest that PAT might lead to a decrease in alcohol consumption without necessarily inducing complete abstinence [15, 54]. We opted for a primary clinical outcome measure at four weeks posthospital discharge to limit attrition, as well as because the literature suggests that at least 50% of patients resume excessive heavy drinking within the first month following an inpatient detoxification program [3, 97]. Longer term follow-up data will be collected up to six months posthospital discharge (see secondary outcomes). The TLFB [68] will be used to measure alcohol consumption. The TLFB is a semi-structured interview designed to assess daily alcohol (and other drug) use by obtaining estimates of quantity, frequency, and usage patterns within a specific timeframe. The tool has demonstrated adequate to excellent reliability and validity [98, 99]. See Table 1 for an overview of key outcomes and sampling time points.

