### Data analysis

The data will be analyzed according to a statistical analysis plan that will be uploaded on ClinicalTrials.gov before unmasking. Significance levels for all analyses will be set at 0.05. Clinical outcome analyses (alcohol consumption parameters) will be performed on the intention-to-treat population, including all randomized patients who have completed the dosing session (visit 7). Changes in continuous outcomes will be analyzed with mixed-model analysis of variance with Helmert contrasts when indicated. For time series analysis, general linear mixed models will be used in the case of missing data. Mediation analyses will be used to evaluate whether hypothesized mechanistic variables mediate the effect of treatment on clinical improvements, for example, whether the mystical experience score during psilocybin administration mediates the impact of treatment on changes in the percentage of heavy drinking days. Treatment-emergent adverse events will be classified, tabulated, and treatment groups contrasted using Chi squared or Fisher’s exact test.

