## Discussion

Although our study aims to address limitations that have been raised within PAT research while investigating questions that currently remain unanswered, some issues might arise from our design. First, the choice to opt for an active placebo group that receives a low yet psychoactive dose of 5 mg of psilocybin involves some risks. Although we hope to maintain blinding or at least increase group allocation ambivalence and therefore reduce the bias induced by large placebo and nocebo effects in the experimental and control groups, respectively, we might be unsuccessful. It is unclear to what extent the effects of a low dose might be mistaken for those of a high dose, and this might depend on individual factors such as past psychedelic experience and sensitivity to psychedelic effects. Moreover, our approach might decrease the effect sizes pertaining to group differences, as even low doses of psilocybin show considerable occupancy of cortical 5-HT_2A_Rs [116] and may therefore induce a therapeutic effect.

Second, while our trial aims to be pragmatic and include a more representative, diverse pool of participants by recruiting directly from within the hospital, we must adhere to safety guidelines and respect strict and rather restrictive inclusion and exclusion criteria, which limits the range of individuals we can include.

Third, as we propose the experimental treatment integrated within a real-world clinical pathway, participation may influence patients’ relationships with other inpatients not included in the study, which might impact social relations during detoxification, thereby affecting treatment trajectory.

Last, our study includes a single dosing session, which might not be enough. Contemporary clinical studies have involved one to three dosing sessions (e.g., [38, 39, 117]), with two psilocybin sessions proposed in the only RCT of PAT for AUD [15]. Interestingly, important decreases in the number of heavy drinking days were already observed after the first session, suggesting a therapeutically significant effect of a single administration. An ongoing trial compares the clinical efficacy of one versus two dosing sessions on major depressive disorder with co-occurring AUD (NCT04620759), which will inform the development of future interventions.

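### The 90% power holds for a 1.0 SD between-arm difference in change, not for a medium effect comparable to the cited g = 0.52

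*Protocol article*

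**What the plan says.** The Sample size section of the protocol article cites two prior effects, "Cohen’s d = 1, [54]; Hedges’ g = 0.52 [15", and describes them as medium to large. In line with these, it says "the sample size was calculated to observe a medium-size effect (Cohen’s f = 0.25) with a power of 0.9" and a type I error of 0.05. The model behind the calculation is a "mixed-design analysis of variance, two groups: high dose vs. active placebo; two timepoints", comparing the percentage of heavy drinking days before hospitalisation with that in the four weeks after discharge. The result is 46 evaluable participants, raised to 62 for 25% attrition. Inclusion continues, if attrition is higher, until 46 have completed visit 14.

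The Primary clinical outcome section defines the contrast: "The primary clinical outcome is the difference between the two treatment arms in terms of change from baseline" to four weeks after discharge. In a two-group, two-timepoint model this is the group-by-time interaction. The section does not give the correlation between the two timepoints, and it does not translate f into a between-arm difference.

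**The concern.** The familiar equivalence of f = 0.25 with d = 0.5 belongs to a plain comparison of two group means. The protocol applies f = 0.25 to an interaction, where the same f corresponds to a between-arm difference twice as large. Because the sentence sets f beside a d and a g, a reader will take it that the trial has about 90% power near the cited randomised estimate of 0.52. If that is untrue, the central efficacy contrast of a superiority trial is described as having a sensitivity it lacks. A non-significant result could then be taken as well-powered evidence against a medium effect.

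**Working it through.** **Inputs.** From the Sample size section: f = 0.25, power 0.9, alpha 0.05, two groups, two timepoints, n = 46, 25% attrition, n = 62, d = 1 and g = 0.52. Allocation is 1:1 (Trial design and study setting). The correlation rho between timepoints is not stated and has to be inferred.

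**Step 1. Reproduce the plan's figure.** For the within-between interaction with m = 2 timepoints, the noncentrality is lambda = f² x N x m / (1 - rho), on 1 and N - 2 degrees of freedom. With rho = 0.5 and N = 46:

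lambda = 0.0625 x 46 x 2 / 0.5 = 11.5, and power = 0.912.

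N = 44 gives 0.8997, so 46 is the smallest even N that reaches 0.90. For attrition, 46 / 0.75 = 61.3, rounded up to 62. Both published figures match.

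Alternatives do not return 46:

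| Calculation at f = 0.25, power 0.9 | N |
|---|---|
| Interaction, rho = 0.4 | 54 |
| Interaction, rho = 0.5 | 46 |
| Interaction, rho = 0.6 | 36 |
| Between-subjects main effect, rho = 0.5 | 130 |
| f = 0.25 applied to the change score (d = 0.5) | 172 |

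**Step 2. Convert f to a between-arm difference.** Let D be the between-arm difference in change and SD the per-timepoint standard deviation. In a 2 x 2 design each of the four interaction cell effects is plus or minus D/4, so f = D / (4 x SD). Hence f = 0.25 gives D = 4 x 0.25 x SD = 1.0 SD. In raw SD units this does not depend on rho.

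The SD of the change score is SD x sqrt(2 x (1 - rho)). At rho = 0.5 this equals SD, so the standardised difference on the change score is also 1.0. As a cross-check, a two-sample t test on change scores with 23 per arm and d = 1.0 gives power 0.912, and simulation gives 0.914.

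**Step 3. Power at the cited randomised estimate.** A difference of 0.52 SD is f = 0.52 / 4 = 0.13. With rho = 0.5:

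- N = 46: lambda = 0.0169 x 46 x 2 / 0.5 = 3.11, power 0.407 (simulation 0.412).
- N = 62: lambda = 0.0169 x 62 x 2 / 0.5 = 4.19, power 0.522.
- For d = 0.5 (f = 0.125): 0.382 with 46 and 0.491 with 62.

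Ninety percent power would need 158 completers at 0.52, or 172 at 0.50.

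**Step 4. Dependence on rho and on the scale of g.** If g is in change-score SD units, the values in Step 3 hold at any rho. If g is in raw SD units, they vary:

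| rho | Power at 0.52, N = 46 | Power at 0.52, N = 62 |
|---|---|---|
| 0.3 | 0.308 | 0.399 |
| 0.5 | 0.407 | 0.522 |
| 0.6 | 0.487 | 0.615 |
| 0.7 | 0.605 | 0.739 |
| 0.8 | 0.778 | 0.890 |

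With 46 completers, power reaches 0.90 only near rho = 0.86. A correlation that high cannot be what the authors used: at rho = 0.8, f = 0.25 would already have needed only 20 participants.

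**The case against.** **The arithmetic is right.** The section states f explicitly, never says d = 0.5, and 90% power at f = 0.25 with 46 completers is correct. This stands. A reader might infer that the power calculation itself is wrong, and the documents do not support that. The error is in what f = 0.25 is taken to mean on the interaction, next to a d and a g.

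**d = 1 is among the cited effects.** This also stands: the design is powered for the top of its cited range. It is not powered for the other cited value or for a medium effect on that scale. It is tempting to discount d = 1 because the study appears elsewhere as "The first contemporary pilot trial of PAT for AUD [54", with effects that still need replication. That remark concerns craving, motivation to change and abstinence self-efficacy, not drinking, so it does not bear on d = 1.

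**The 40% figure is conditional.** This is correct. The scale of the cited g cannot be checked from the document, rho is inferred, and the Data analysis section analyses everyone dosed, so more than 46 may contribute. These points widen the range shown above. They do not restore 90% over correlations from 0.3 to 0.8.

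**The comparator.** The Discussion says that "our approach might decrease the effect sizes pertaining to group differences". A reader might infer that the authors expect a smaller effect. The text only raises it as a possibility.

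**Is 1.0 SD attainable?** A reader might also infer that so large a difference is out of reach for this outcome. The document gives no SD for the percentage of heavy drinking days, so this cannot be judged from it.

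**Preliminary aim.** The trial seeks feasibility and preliminary efficacy, with safety and feasibility also primary. That is a good reason not to demand a larger trial, but it does not justify the medium-size label.

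**Conclusion.** The concern holds as a misinterpreted effect size, not as a computational error. The 46 completers give about 90% power for a between-arm difference in change of 1.0 SD, about twice the cited randomised estimate (1.0 / 0.52 = 1.9). At 0.52 the power is about 41% with 46 completers and 52% with 62, if g is in change-score SD units or rho = 0.5. If g is in raw SD units, power with 46 lies between 31% and 78% for rho from 0.3 to 0.8.

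The conclusion rests on three assumptions: that the test is the group-by-time interaction, as the primary outcome implies; that rho was about 0.5, the only value tried that returns 46; and a two-sided 0.05 level ("Significance levels for all analyses will be set at 0.05"). The equivalence of f = 0.25 with 1.0 raw SD needs only the first. Under the central assumptions the trial would miss an effect of 0.52 more often than detect it with 46 completers.

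**What to change.** In the Sample size section, replace the description of a medium-size effect with wording such as: 46 completers give about 90% power for a between-arm difference in change of about 1.0 SD (interaction f = 0.25, assuming a correlation of 0.5 between timepoints), and about 40% power for a standardised difference of 0.52 on the change score.

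Carry the same statement into any registry or analysis-plan text that repeats the power claim, and do not interpret a null result as evidence against a medium effect.

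The cost is rewording only, with a less favourable figure on display. Enrolment, the primary analysis and trial conduct stay as they are, and no increase in sample size is required.

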#### Screening and eligibility

Candidate participants must provide written informed consent before being screened for eligibility. The screening process will consist of a neuropsychiatric screening and a physical screening taking place across two visits. Alcohol consumption will be recorded at both visits using the Timeline Follow-Back method (TLFB; [68]) to obtain a baseline measure. The final decision on eligibility will be made by medical doctors only.

Candidate participants will have to comply with the following key eligibility criteria:

Key inclusion criteria

Age of 21–64 years,BMI between 17.5 and 30 kg/m^2^,Desire to stop or decrease drinking,Have a diagnosis of severe alcohol use disorder (sAUD), according to the DSM-5-TR (6 criteria or more),Undergoing a 4-week alcohol detoxification program at the Brugmann University Hospital,Women of childbearing potential must be using an effective, established method of contraception from inclusion until four weeks posthospital discharge (5 weeks post-psilocybin administration),Men with a woman of childbearing potential should use a condom during intercourse from inclusion until four weeks posthospital discharge (5 weeks post-psilocybin administration).

Key exclusion criteria

Cardiovascular, hepatic, gastroenterological, hematologic, renal, endocrine, metabolic, inflammatory, or neurological diseases or any other somatic condition that, in the opinion of the medical investigator, would pose a risk to the participant’s participation in the study,Serious abnormalities of complete blood count or chemistries, biological abnormalities including TP < 50%, albumin < 35 g/L, total bilirubin > 35 µmol/L, leading to a Child B or C score,Cognitive impairment (Folstein Mini Mental State Exam [69] score < 26),Alcohol withdrawal complication(s), seizure, head injury or stroke within the last 6 months,Current active acute stress disorder/posttraumatic stress disorder,Lifetime history of schizophrenia spectrum disorders, other psychotic disorders, or bipolar spectrum disorders,Significant risk of suicide according to clinician assessment,Family history of schizophrenia spectrum disorders, other psychotic disorders, or bipolar I disorder in first- or second-degree relatives,Other substance use disorder (except for caffeine, nicotine, or cannabis) according to DSM-5-TR criteria in the two months preceding inclusion,Severe cannabis use disorder according to the DSM-5-TR,Need to take medication with significant potential to interact with psilocybin,Pregnancy and breastfeeding, at screening visit and until dosing day.

### Clinical intervention

Our trial will compare a single administration of either 30 mg of psilocybin (high dose) or 5 mg of psilocybin (active placebo) embedded in a supportive psychotherapy protocol integrating key elements of ACT [70] within the context of a four-week inpatient alcohol detoxification program. Pharmaceutical-grade psilocybin is provided in the form of capsules by Psilo Scientific Ltd. (Wholly Owned Subsidiary Of Filament Health Corp.).

#### Dose rationale

The optimal therapeutic dose of psilocybin in the treatment of sAUD has not been determined. While in the only published contemporary RCT of PAT for AUD, a second dose of up to 40 mg/70 kg was administered (following a first dose of 25 mg/70 kg, [15]), all currently ongoing trials in this population have opted for one to two doses of 25 mg (NCT04141501, NCT05416229, NCT05646303, NCT04620759, and NCT04410913). Of note, relative doses have been mostly substituted with absolute doses, following evidence that body weight has no influence on psilocybin pharmacokinetics [71] and subjective effects [72] in humans. There may be some advantages to selecting a higher dose of 30 mg. First, preclinical evidence suggests a dose-dependent effect on increases in the expression of some neuroplasticity-related genes induced by serotonergic psychedelics [73–75], a key proposed therapeutic mechanism [44, 45]. Second, phase I and II studies suggest a dose-dependent effect on the quality of the psychedelic experience [54, 76], with high mystical experience scores associated with 30 mg/70 kg of psilocybin [76], another proposed therapeutic mechanism [77]. Last, early studies with LSD and contemporary studies with psilocybin suggest that patients with AUD may tend to display more tolerance to serotonergic psychedelics, whereas high doses of 30–40 mg/70 kg are well tolerated in this population [15, 54, 78].

#### Explanation for choice of comparator

We decided to opt for a design in which the control group receives a low yet psychoactive dose of psilocybin (5 mg, [76]), which would theoretically not induce significant clinical benefits (e.g., [38] observed a significant decrease in depression symptomatology in participants with treatment-resistant depression after a single 25 mg dose relative to a 1 mg dose, but not with a 10 mg dose), while it may adequately maintain blinding (5 mg of psilocybin was shown to induce subjective changes significantly greater than those of an inert placebo; [76]). A complementary measure to enhance blinding will consist of an emphasis on the substantial interindividual and intersituational variability in response to psilocybin to increase ambivalence. Last, blinding efficacy (participants, therapists) and expectancy (participants) will be assessed and reported, as recommended in the literature [32–34].

#### Benzodiazepine discontinuation

Benzodiazepines with a short half-life (lorazepam [79]) will be used for the treatment of acute alcohol withdrawal syndrome upon admission in the inpatient alcohol detoxification program. The shorter half-life allows us to minimize the potential benzodiazepine-psilocybin interaction by ensuring a relatively lower lorazepam plasma concentration rapidly after full tapering off (at least 3 days before psilocybin administration), which is relevant, as benzodiazepines might blunt the psychedelic experience. The Clinical Institute Withdrawal Assessment Alcohol Scale Revised (CIWA-AR; [80]) will be used to assess withdrawal symptoms to ensure safe progressive lorazepam discontinuation, in line with evidence-based practice guidelines recommending individualized tapering off schedules with withdrawal scales [81]. In case full tapering off from lorazepam cannot be achieved within 17 days due to withdrawal symptoms, participants will be excluded from the study.

#### Behavioral intervention

Both treatment arms will be provided in the context of a three-part psychotherapeutic intervention, involving two preparation sessions, support during the psilocybin dosing session, and two integration sessions, all conducted during the four-week inpatient care. The sessions will be conducted by a mixed-gender therapist dyad. The leading therapist must hold a master’s degree in a related field (psychiatry, psychology) and a minimum of three years of experience with psychiatric patients in a clinical setting. The co-therapist must hold a master’s degree in a related field or be in their ultimate or penultimate year in pursuing such a degree. All therapists will be required to read the entire study manual, attend a study-specific training workshop, and attend supervision sessions by a designated lead therapist.

Although contemporary clinical trials have invariably provided preparation and integration sessions before and after psilocybin administration, respectively, the theoretical orientation and frequency of these sessions have varied across trials (see [82] for a review). Relatedly, the optimal model to maximize PAT efficacy is yet to be clarified. For our study, we decided to opt for a theory-driven, manualized procedure that incorporates principles of ACT, an approach with demonstrated efficacy in the treatment of AUD [83, 84]. Our manual is adapted from the Yale Manual for Psilocybin-Assisted Therapy of Depression [85] to fit our target population (patients with sAUD) and our study design.

ACT integrates radical behaviorism with experiential methods to address transdiagnostic factors that contribute to psychological suffering, including fusion with thoughts, evaluation of experiences, avoidance, and reason-giving [86]. To transcend these psychological processes, ACT aims to foster psychological flexibility through six key processes: present moment awareness, acceptance, defusion, value clarification, committed action, and the development of a flexible sense of self [86]. The rationale for integrating ACT principles into the PAT model stems from the proposed concordance between mechanisms of change generated by both approaches, as the psychedelic experience may provide direct experiential access to key ACT processes known to enhance psychological flexibility (see [87] for an in-depth discussion).

